### Secondary outcome measures

Static balance ability will be measured by the single-leg stance test (SLST) and Romberg’s test.Dynamic balance ability will be measured by the Timed Up and Go test (TUG) and functional reach test (FRT).Cognitive ability will be measured by the Chinese version of the Montreal Cognitive Assessment scale.Physical frailty will be measured by the Chinese version of the Edmonton Frailty Scale.Fear of falling will be measured by the Modified Fall Efficacy Scale.Lower extremity muscle strength will be measured by the 30-s chair stand test (CST).Hand grip strength will be measured by an electronic grip force meter.

The SLST is widely used to assess static balance ability in older adults and has normative data accepted by the scientific literature [33]. Romberg’s test evaluates balance ability by having individuals stand as much as possible without deviating from the standing position, regardless of foot position and different visual conditions (i.e., eyes open/eyes closed) [34].

The TUG test is utilized for the evaluation of functional mobility involving velocity, potency, and dynamic balance and is a common test to assess gait stability and balance in older adults [35], while the FRT is also a valid test in the assessment of balance in older adults by measuring the limits of stability of individuals while reaching forward in a standing position, in which the limits of stability are defined as the maximum distance that the centre of mass can be moved safely without changes in the base of support [36].

The Chinese version of the Montreal Cognitive Assessment Scale (MoCA) is a brief cognitive screening test that covers eight cognitive domains, including visual spatial ability and execution, naming, memory, attention, language, abstraction, delayed recall, and orientation, with good validity and sensitivity in the Chinese population [37].

The Edmonton Frailty Scale (EFS) consists of nine domains, such as cognition, basic health, independence, social support, drug use, nutrition, mood, control, and function performance, with good interrater reliability (k = 0.77) [38].

The Modified Falls Efficacy Scale (MFES) will be used to assess fear of falling by measuring confidence in performing a range of specific activities of daily living associated with an increased risk of falling. It is a well-established measure with acceptable reliability, validity, and sensitivity in different older people [39].

The CST is a functional test of lower extremity muscle strength of older adults that measures their ability to rise from a chair and is also involved in other functional domains, such as balance, coordination, and endurance [40].

Hand grip strength is an indicator of upper body strength and is also an indicator of overall muscle strength in the community-dwelling older population [41], which will be measured using an electronic grip force meter (CAMRY-EH101).

## Adverse events

Participants will be supervised for adverse events during the intervention. The research assistant will describe and report the adverse events to research group by the adverse event report form. The medical monitor and research group will evaluate each adverse event and classify it by severity (mild, moderate, severe/undesirable, potentially life threatening or death) and by grading (unrelated, possibly related, or definitely related). If serious adverse events occur, it will be reported to the ethics committee immediately.

## Statistical analysis

Data will be analysed according to the intention-to-treat principle (ITT) using the SPSS 21.0 software package by an independent statistician, with a statistical significance of *p* < 0.05 on both sides. Missing data will be complemented using the multiple imputation method.

Descriptive statistics will be performed using the mean and standard deviation (SD)/median and interquartile ranges for continuous outcomes or percentages for categorical outcomes. Baseline characteristics will be compared between the Baduanjin exercise training group and the control group to identify the adequacy of randomization and possible confounders. We plan to analyze primary and secondary outcomes using the mixed-effect linear model with restricted maximum likelihood, and group (Baduanjin exercise training and the control group), time (baseline and after intervention) and possible confounding factors will be introduced into the model as independent variables.

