## Sample size calculation

Sample size was calculated based on the group mean comparison formula by using the effect size of the primary outcome (mini-BESTest scores) from the study conducted by Ni M et al. [27]. Considering 80% efficacy and 5% I type error (two tails), at least 30 subjects in each group were enough to detect the target effect mini-BESTest changes between two groups. Considering a 20% dropout rate, 36 subjects each group are planned to be recruited in this trial. Calculations were performed using Gpower 0.3.1.6.2 software.

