### Baseline assessment

Baseline information of all eligible participants will be collected by the recruiters using a self-designed questionnaire. Baseline information includes the participants’ personal general data and demographic information, such as gender, age, height, weight, years of education, marital status, occupation, medical history, lifestyle, diet, and physical activity.

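### Covariates are to be chosen by comparing the randomised arms at baseline, which cannot identify confounders; name them in advance on prognostic grounds and adjust for the baseline score

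*Protocol article*

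**What the plan says.** The Statistical analysis section of the protocol article gives the route by which covariates reach the model. First, "Baseline characteristics will be compared between the Baduanjin exercise training group and the control group to identify the adequacy of randomization and possible confounders". Then, for the model itself, "We plan to analyze primary and secondary outcomes using the mixed-effect linear model with restricted maximum likelihood", with group, time and confounders as predictors: "possible confounding factors will be introduced into the model as independent variables". No covariate is named, no cut-off is given, and prognostic strength is not mentioned as a reason for adjustment. The comparison of arms is the only selection route stated.

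The same section makes baseline one of the two levels of the time factor. The baseline score is thus in the model as a repeated response, not as a covariate, and no group-by-time term is listed.

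The candidate variables appear under Baseline assessment: "such as gender, age, height, weight, years of education, marital status, occupation, medical history, lifestyle, diet, and physical activity". That is 11 kinds of variable, introduced as examples. The Randomization, allocation concealment, and blinding section says that the statisticians will be blinded.

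**The concern.** With random 1:1 allocation, a baseline difference between arms is a chance event unless the allocation procedure itself failed. Comparing the arms therefore answers neither question put to it. It does not show whether allocation was carried out properly, and it does not reveal confounding.

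The comparison is also a poor way to choose covariates. What adjustment gains depends on how strongly a variable predicts the outcome. A strong predictor that happens to be balanced would be left out, and an irrelevant variable that happens to differ would go in.

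Two things are at stake. One is precision, in a trial of 72 people sized at 80% power. The other is that the primary model is not settled until the data have been seen. With no stated threshold, several models would be equally faithful to the protocol.

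**Working it through.** **Inputs from the article.** Two-sided 5% error, 80% power and 30 per arm before dropout (Sample size calculation); 11 kinds of baseline variable (Baseline assessment).

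**Assumptions not in the article.** The correlation ρ between baseline and follow-up score, taken as 0.3, 0.5 and 0.7; equal variances at the two visits; a 5% screening threshold; independent baseline variables.

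**1. Effect size implied by the sample size.** The 30 per arm cannot be reproduced forwards, because the effect size is taken from a cited study and not printed. Solving backwards with the normal formula:

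d = (1.960 + 0.842) × √(2/30) = 0.723

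The noncentral t version gives 0.736.

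**2. How often chance alone would supply a "confounder".** For 11 independent variables screened at 5%:

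1 − 0.95^11 = 0.43

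So in about 43% of correctly randomised trials at least one variable would be flagged. The expected number is 11 × 0.05 = 0.55. Both figures only illustrate how the model would vary with chance, since the article states neither the threshold nor that all 11 are screened.

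**3. Type I error under a fixed screen.** In 4,000 simulated trials per scenario (30 per arm, baseline score plus 10 other covariates, one of them prognostic, entry if baseline p < 0.05), the rejection rate under no effect was as follows.

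| ρ | Follow-up score, screened covariates | Change score, screened covariates |
|---|---|---|
| 0.5 | 3.6% | 4.3% |
| 0.7 | 3.2% | 4.8% |

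There is no inflation, and the screen is slightly conservative.

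**4. Type I error with discretion.** In a separate simulation (6,000 trials, follow-up score, 11 covariates of which two are prognostic), reporting the most favourable of four analyses (unadjusted, and screens at 0.05, 0.10 and 0.20) gave about 6%. The excess over 5% comes from choosing among models, not from the screen.

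**5. Precision given up on the baseline score.** Relative to a follow-up-only analysis, the variance factors are 2(1 − ρ) for a change-type contrast and 1 − ρ² with baseline as a covariate. Their ratio is 2(1 − ρ)/(1 − ρ²) = 2/(1 + ρ). Power is Φ(0.723 × √(30/2) / √factor − 1.960), and 0.723 × √15 = 2.80.

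| ρ | Change factor | Power, change | Covariate factor | Power, baseline as covariate | Variance ratio |
|---|---|---|---|---|---|
| 0.3 | 1.40 | 66% | 0.91 | 84% | 1.54 |
| 0.5 | 1.00 | 80% | 0.75 | 90% | 1.33 |
| 0.7 | 0.60 | 95% | 0.51 | 97.5% | 1.18 |

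For example, at ρ = 0.5 with baseline as a covariate: 2.80/√0.75 = 3.23, 3.23 − 1.96 = 1.27, and Φ(1.27) = 0.90. A follow-up-only analysis has 80% throughout, by construction.

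**6. What main-effect covariates do in the stated model.** Suppose the effect is read from a group-by-time contrast with baseline means free in each arm. With complete data on two visits, that contrast is the difference between arms in mean change. A covariate with the same effect at both visits cancels from each person's change, so it leaves the estimate unaltered. If the effect is read from the group term that the article lists, covariates can move it. Under neither reading does selection by imbalance bring a justified gain.

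**The case against.** **The selection rule is partly inferred.** The article says only that the arms will be compared. It does not mention tests, a 5% cut-off or screening all 11 variables, and some of them (gender, height and weight, for instance) are plainly correlated. This stands, so the 43% is an illustration and not a property of this trial. The logical fault does not depend on any cut-off.

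**The error rate.** A reader might infer that the test loses its nominal error rate. The documents do not support that. A fixed screen gives 3–5%, and exceeding 5% requires someone to choose between models. The analysis is assigned to an independent statistician, and the statisticians are blinded, which limits steering towards a favoured arm. It does not remove the choice, since models can be compared with coded arms.

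**The size of the loss.** A reader might infer a loss of about 12 percentage points of power, from simulations that give about 80% with screening and 92% with two prognostic covariates fixed in advance. Those use ordinary regression on the follow-up score and invented covariate strengths (0.5 and 0.3). They do not represent the stated mixed model, where the baseline score is already a repeated response and main-effect covariates may not touch the contrast at all. Nor can one say that the baseline score is ignored; it is used, but less efficiently than it could be.

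**An unseen analysis plan.** Naming covariates is often left to that document, and their absence from a journal article is no fault. But the article does state how covariates will be found, and an analysis plan that follows it inherits the problem.

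**Prognostic value.** The article gives no evidence that age, gender or education predicts the balance scores. This stands, so the sponsor should justify the set that it names.

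**Conclusion.** The point holds as a badly fixed selection rule. Comparing randomised arms at baseline can neither confirm the randomisation nor identify confounders, and using it to build the primary model ties that model to chance imbalances. The trial remains valid and a mechanical screen would not raise its type I error. The costs are forgone precision and avoidable discretion.

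The precision cost is conditional. Against a change-type contrast, adjustment for the baseline score would add about 18 points of power at ρ = 0.3 (66% to 84%), 10 at 0.5 (80% to 90%) and 2.5 at 0.7 (95% to 97.5%). These gains rest on 30 evaluable per arm, a back-solved d of about 0.72, equal variances at the two visits and assumed correlations. They also assume that the effect would be read as a change-type contrast. Any gain from other covariates cannot be sized from the article. The change should be made, and it should be made before unblinding; recruitment was already complete when the article was submitted.

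**What to change.** 1. Delete the selection step. Present the baseline table descriptively, and do not use it to judge the randomisation or to choose covariates.
2. Before unblinding, fix the primary model in one of two forms. The first is follow-up score on group, adjusted for the baseline value of the same outcome. The second is the mixed model with a common baseline mean for both arms and a group-by-time contrast. The baseline score should not be both a response and a covariate in the same model.
3. Add a short covariate set named on prognostic grounds from what is already collected, for example age, gender and years of education, plus community centre, and give the grounds for each.
4. If the repeated-measures form is kept, let these covariates interact with time. With baseline means free in each arm, main effects alone leave the group-by-time contrast unchanged in complete data. With a common baseline mean, they force the same covariate effect at both visits.
5. Label any other adjustment as a sensitivity analysis.

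No new data are needed. The cost is a changed model statement, which is more than a wording edit because the role of the baseline score changes, and a few degrees of freedom.

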## Outcome measures

In this trial, the primary and secondary outcomes will be measured at baseline (1–2 weeks before randomization) and at the end of the 24-week intervention period (25 weeks after randomization). All outcome assessments will be independently conducted by experienced and blinded assessors. A summary of all measurements in this trial is shown in Fig. 2.

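### With baseline fitted as an outcome row and the treatment contrast unnamed, the planned confounder adjustment either cancels out of the difference in change or acts on a diluted two-visit average

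*Protocol article*

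**What the plan says.** All of this is in the Protocol article.

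- **Model (Statistical analysis).** "We plan to analyze primary and secondary outcomes using the mixed-effect linear model with restricted maximum likelihood". The independent variables are group, "time (baseline and after intervention) and possible confounding factors will be introduced into the model as independent variables". Because time has a baseline level, the baseline score is a response. No group-by-time or confounder-by-time term is written, and no coefficient is named as the treatment effect.
- **Source of the confounders (Statistical analysis).** "Baseline characteristics will be compared between the Baduanjin exercise training group and the control group to identify the adequacy of randomization and possible confounders". They are baseline characteristics, so each is constant within a participant.
- **Missing data (Statistical analysis).** "Missing data will be complemented using the multiple imputation method".
- **Visits (Outcome measures).** "the primary and secondary outcomes will be measured at baseline (1–2 weeks before randomization) and at the end of the 24-week intervention period". There are two measurements per participant.
- **Target (Sample size calculation).** The target is described as a between-group effect on change in the Mini-BESTest. "Considering 80% efficacy and 5% I type error (two tails), at least 30 subjects in each group were enough", raised to 36 per group for dropout. The effect size itself is not printed.

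**The concern.** The article compares the arms at baseline to find confounders and then puts them in the model, so adjusting the treatment effect is a stated purpose. A covariate that is fixed within a person and enters as a main effect shifts both of that person's rows equally. It can explain differences in level between people, but it cannot alter a contrast in change.

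The trial could therefore report an effect labelled as adjusted that is identical to the unadjusted one, or an adjusted coefficient that is not the end-of-intervention effect. With 36 per arm, some chance baseline imbalance is to be expected, and the baseline scores that could deal with it are already being collected. Choosing better covariates, or adding only the group-by-time term, would not cure this.

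**Working it through.** **Inputs.** From the article: two visits, 36 per arm planned, 30 per arm before dropout, 80% power, two-sided 5%. Assumed: baseline/follow-up correlation r between 0.5 and 0.8, equal SDs at both visits, and a sample size effect standardised on the change score.

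**1. Group-by-time reading.** For participant i at time t (0 or 1), with arm G and baseline covariate X:

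Y(i,t) = a + b·G + c·t + d·G·t + θ·X + u(i) + e(i,t)

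Subtracting the rows gives Y(i,1) − Y(i,0) = c + d·G + e(i,1) − e(i,0). The term θ·X is gone. With both rows present for everyone, the estimate of d is the raw difference in mean change, with or without X. Each imputed data set is complete, so the identity holds in each one and in the pooled estimate. (Covariates may still influence the imputed values, but that is not adjustment in the analysis model.)

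Simulation check: 36 per arm, true effect 3, covariate slope 1.5, between-person SD 2.5, residual SD 2, random-intercept REML. Over 150 trials, adding the covariate main effect changed the estimate by at most 0.000000 and its SE by at most 0.00002.

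Two single data sets with a covariate imbalance of 0.5 SD show which analyses respond to the covariate. They do not show which is closer to the truth.

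| Estimate | Covariate acts equally at both visits | Covariate also affects change |
|---|---|---|
| Group × time, no covariate | 3.179 | 2.110 |
| Group × time, covariate main effect | 3.179 | 2.110 |
| Group × time, covariate × time added | 3.203 | 1.440 |
| ANCOVA on baseline, no covariate | 3.277 | 2.164 |
| ANCOVA on baseline, with covariate | 3.187 | 1.404 |

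**2. Literal reading (group + time + confounders).** With complete rows the group coefficient is (D0 + D1)/2, where D0 and D1 are the between-arm differences at baseline and week 25. Under randomisation D0 has expectation zero, so the coefficient targets half the week-25 effect. In the first data set D1 = 3.468 and D0 = 3.468 − 3.179 = 0.289, so the average is 1.878, which is the fitted value. Over 150 trials without built-in imbalance it averaged 1.41 for a true effect of 3. Adjustment does move it: 1.878 to 1.559 in the first data set, 1.727 to 0.637 in the second, and a mean absolute change of 0.30 over the 150 trials.

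**3. Conditional bias of difference in change.** Given a baseline difference δ, the change estimate is shifted by (1 − r)·δ in size. The SD of δ by chance is √(2/36) = 0.236 outcome SD.

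- 1-SD imbalance: 0.236 × 0.3 = 0.07 at r = 0.7; 0.236 × 0.5 = 0.12 at r = 0.5.
- 2-SD imbalance: 0.14 to 0.24.

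The article's effect size cannot be reproduced. A t-test with 30 per arm and 80% power implies d = 0.736 on the change-score SD. In outcome SDs this is 0.736 × √(2(1 − r)), or 0.736 at r = 0.5 and 0.570 at r = 0.7. A 2-SD imbalance is then 0.141/0.570 = 25% to 0.236/0.736 = 32% of the implied target.

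**4. Power.** The variance is proportional to 2(1 − r) for change and to 1 − r² for ANCOVA, so the standardised effect grows by √(2/(1 + r)). At 30 per arm:

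| r | Factor | Standardised effect | Power |
|---|---|---|---|
| 0.5 | 1.155 | 0.849 | 90% |
| 0.6 | 1.118 | 0.822 | 88% |
| 0.7 | 1.085 | 0.798 | 86% |
| 0.8 | 1.054 | 0.775 | 84% |

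**The case against.** The strongest reply is that the article writes no group-by-time term, so exact cancellation applies to a contrast it does not state, while under the terms it does list adjustment moves the between-arm coefficient. It is also fair that the article never says confounders enter only as main effects. A journal article condenses, and interactions may be specified elsewhere. Both points stand, and they make the finding conditional. A reader might infer that adjustment changes nothing under any reading; step 2 shows otherwise. They do not rescue the plan as printed, because the coefficient that adjustment does move is a two-visit average.

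Second, difference in change is a legitimate estimator. It is unbiased over randomisation and already subtracts the baseline outcome difference. For a covariate acting equally at both visits nothing much is lost (3.179 against 3.203). This stands too. The shift in step 3 is conditional on the imbalance that occurs, and the document has no evidence on which covariates predict change.

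Third, ANCOVA against baseline-as-response may be called a preference. In part it is, and the power gain is an improvement on the planned 80%, not an error in it. But the article sets out to adjust the effect, and the listed model does not do so for the end-of-intervention difference.

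A reader might also infer an inflated type I error. That would require the baseline score of the outcome to be entered as a covariate while it is also a response. The article does not name that score among the confounders, so this is not supported.

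**Conclusion.** The point holds in conditional form. Baseline is fitted as an outcome row and the treatment contrast is not named.

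- If the effect is the difference in change, main-effect confounders do not alter it. This is exact, given a free group main effect, time-constant covariates and complete rows. With unimputed missing week-25 rows the estimate moved slightly in one simulated data set (3.797 to 3.709).
- If the listed terms are fitted literally, the adjusted coefficient captures about half the effect.

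Under neither reading is the week-25 difference adjusted as intended. The consequence is moderate: 0.07 to 0.12 SD of conditional bias for a 1-SD chance imbalance, and power of 80% where about 84% to 90% is available from the same data. These figures rest on the assumed correlations and, for power, on the stated 80% applying to change. The change should be made, but the planned analysis is not invalid over repeated randomisation.

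**What to change.** Before unblinding, specify for each continuous outcome an ANCOVA with the week-25 score as the only response, and arm, the baseline value of the same outcome and the covariates as independent variables. Alternatively, keep two rows but constrain the arms to a common baseline mean (time and arm-by-time, no arm main effect) and enter each covariate together with its covariate-by-time term. In either case, state that the treatment effect is the adjusted week-25 between-arm difference.

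The cost is a few lines of analysis wording. No new data, visits or participants are needed, since the baseline scores are already collected. If a fuller plan already contains these terms, quoting them in the article's wording closes the point.
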